### Health economic evaluation

This economic evaluation will be a cost-effectiveness analysis, and the primary objective is to explore the cost-effectiveness of a psychological service model designed specifically for acute mental health wards. This economic analysis will be conducted from the societal perspective incorporating costs borne by the NHS, personal and social services, criminal justice system and education authorities. This perspective is recommended by the National Institute for Health and Care Excellence (NICE) for interventions with health and non-health outcomes in the public sector and other settings [32].

Quality-Adjusted Life Years (QALYs) will be used as the health outcome measure of the cost-utility analysis. The EQ-5D-5L will be used to assess the health status and to estimate QALYs, using published EQ-5D-5L utility weights for the UK [33]. There is good evidence from previous trials of inpatients that patients can complete EQ-5D and resource use inventories during an inpatient admissions [16, 27]. The decision to use patient-reported health status as opposed to case note review has been made as the majority of patients will have been discharged from hospital at the follow ups and resource use will not necessarily be well documented or easy to locate (for example primary care services, social care services and secondary care services often use different electronic systems to record patient care). Also, previous research with mental health patients exploring differences between patient-reported health status, case note review and observations demonstrates that self-report is a reliable and objective method of collecting information on the therapeutically relevant activities and staff contacts [34, 35].

Healthcare resource use will be collected retrospectively for all included service users by means of a detailed health economic questionnaire adapted to the context of psycho-social ward-based intervention in adult acute mental health wards. The HE measures are completed by research assistants on the wards at baseline and 6 and 9 month follow-ups for both the intervention and control groups. Data collated from the health economic measure will be used to estimate the costs of health and social care service use over the past 3 months, including the current admission or any previous or future admissions and medications administered.

Medical costs that will be assessed include costs of the interventions, inpatient care and medication use. These will be estimated by multiplying resource use data by the relevant unit cost figures. Any unit costs not available for this price year will be inflated to 2019/20 prices using the Retail Price Index (RPI) [36].

Other paramount costs to consider are costs of serious incidents and costs savings resulting from reductions in staff sickness and time spent reporting serious and dealing with serious incidents at the ward level. Staff sickness is routinely recorded by wards and staff will be asked to log time spent in relation to serious incidents as part of the reporting procedure to provide estimates of typical times spent reporting and dealing with each type of incident. Unit costs for each type of service will be derived from local and national databases and statistics. Unit costs of serious incidents are not readily available and would be derived by estimating the resources that are typically used to deal with incidents arising from conflict and containment. Containment costs will be estimated based on the standard time spent by health professionals on containment measures (e.g. verbal/psychological, seclusion, physical restraints, ad-hoc medication). A micro-costing analysis of specific activities or interventions related to containment of serious incidents will be performed from the healthcare provider perspective. Information about containment measures and aggressions will be sourced from hospital databases/records (e.g. number of serious incidents or agitation episodes treated with seclusion or restraints) as it is a normal practice for a ward/hospital to maintain a register for declared serious incidents. Which, among other data, registers the number of aggression towards staff, other patients or self-harm.

Sensitivity analyses will be conducted around unit costs and numbers of incidents as well as different methods of dealing with missing data.

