Other important outcomes to target and assess are distressing mental health symptoms and level of patient social functioning. These will be measured through the Brief Symptom Inventory (BSI; [24]) and Personal and Social Performance Scale (PSP; [25]). Improving these outcomes is not only important for patients and their families, but is likely to reduce length of admission, which in turn has the potential for significant cost savings. A further important outcome is patients’ perceptions of ward atmosphere [7, 11, 26] and previous research has suggested that working with ward staff to help them to deliver more psychologically-informed care can improve patient perceptions of ward atmosphere [27]. Improving patient access to psychological therapies is also likely to have a positive effect on frontline mental health staff who often experience high levels of burnout when working with risky behaviours. Patient and staff perceptions of the ward atmosphere will be assessed using the Views on Inpatient Care (VOICE; [20]) and Views on Therapeutic Environments (VOTE; [28]), respectively.

Staff burnout will be measured using the Maslach Burnout Inventory (MBI; [29]). Additional ward level data, patient resource use, and health-related quality of life measures will support the health economic evaluation.

See Table 1 for further information on who completes which measures in the study and at what time point.

**Table 1 Tab1:** Outcome measures and time-points for collection

**Measures**	**Baseline**	**6 Month** **Follow Up**	**9 Month** **Follow Up**

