**Patient Measures**			
Informed consent	x	x (VOICE participants)	
Demographics	x	x (VOICE participants)	
Brief Symptom Inventory (BSI; Derogatis, 1993)	x	x	x
Personal and Social Performance Scale (PSP; Morosini et al, 2000)	x	x	x
Quality of Life (EQ-5D-5L)	x	x	x
Views on In-Patient Care (VOICE; Evans et al, 2012)		x (VOICE participants)	
Warwick-Edinburgh Mental Well-being Scale (WEMWBS; http://www2.warwick.ac.uk/ fac/med/research/platform/)	x	x (including VOICE participants)	x
Health Economic (HE) Measure	x	x	x

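### A 3-month look-back at baseline, 6 and 9 months leaves patient-reported service use in months 0–3 uncovered, with admissions a possible exception

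*Protocol article*

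**What the plan says.** All references are to the protocol article.

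- **Timing.** Under Health economic evaluation: "The HE measures are completed by research assistants on the wards at baseline and 6 and 9 month follow-ups". The Table 1 row "Health Economic (HE) Measure" is marked at the same three points, and the table has no 3-month column.
- **Look-back.** The same section says the data will be "used to estimate the costs of health and social care service use over the past 3 months". The sentence then widens its list: "including the current admission or any previous or future admissions and medications administered".
- **Effects.** QALYs are to be estimated from the EQ-5D-5L, which Table 1 places at baseline, 6 and 9 months. The QALY horizon is not stated in words.
- **Source.** Resource use comes from a retrospective questionnaire, and the section explains why patient report was preferred to case note review.
- **Other costs.** The section also costs the intervention itself. Serious incidents, containment and staff sickness are to be costed largely from ward or hospital records.
- **Serious incidents.** Under Outcome measures these also have a 3-month look-back, but they are collected at baseline, 3, 6 and 9 months.

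**The concern.** A look-back should reach back at least to the previous visit. Here the gap between the first two visits is 6 months and the look-back is 3, so the first three months after baseline fall between questionnaires.

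Those months matter. Patients are recruited as inpatients just before the intervention starts (Recruitment), and most are expected to have been discharged by follow-up. Months 0–3 are thus likely to contain continuing inpatient care and early care after discharge. Under Outcome measures the protocol expects that improvement in symptoms and functioning "is likely to reduce length of admission, which in turn has the potential for significant cost savings". If the cost of the intervention is counted while patient-level service use in the first half of its delivery is not, the incremental cost is incomplete. Data that were never requested cannot be recovered reliably at analysis. The planned sensitivity analyses on missing data are aimed at answers sought but not obtained, which is a different problem.

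**Working it through.** **Inputs.** Questionnaire visits at months 0, 6 and 9 (Health economic evaluation; Table 1). Look-back of 3 months (Health economic evaluation). Intervention period of 6 months (Intervention). Serious incidents at months 0, 3, 6 and 9 with a 3-month look-back (Outcome measures). Month 0 is taken as the start of the intervention, since patients are recruited just before it.

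**Formula.** A visit at month v with look-back r covers the interval from v − r to v.

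| Visit | Calculation | Window |
|---|---|---|
| Baseline | 0 − 3 | −3 to 0 |
| 6 months | 6 − 3 | 3 to 6 |
| 9 months | 9 − 3 | 6 to 9 |

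**Coverage after baseline.** Covered: 3 + 3 = 6 of 9 months (67%). Not covered: 9 − 6 = 3 months, namely 0–3, and 3/9 = 33%. Within the intervention period the uncovered share is 3/6 = 50%.

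**Comparison with serious incidents.** Visits at 3, 6 and 9 months with the same look-back cover 0–3, 3–6 and 6–9, which is 9 of 9 months. The questionnaire has the same look-back but no 3-month visit.

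**Coverage after the change.** If the 6-month visit looks back 6 months it covers 0–6. With 6–9 from the last visit, coverage is 9 of 9 months.

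**Direction of bias.** Let D be the mean difference (intervention minus control) in the uncollected patient-level costs of months 0–3. The estimated incremental cost is then the true value minus D.

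- If the intervention lowers service use in those months (D < 0), the estimate is too high, which counts against the intervention.
- If it raises service use (D > 0), the estimate is too low.
- If D = 0, the incremental cost is unbiased, though total cost per arm is still understated.

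The document gives no post-baseline length of stay, no service-use rates and no expected difference between arms, so D cannot be calculated.

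**Time horizons.** EQ-5D-5L at 0, 6 and 9 months allows utility to be interpolated over the full 9 months. Patient-level costs, read literally, cover only 3–9.

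**The case against.** The strongest reply is that one summary sentence in a condensed article is thin evidence of what the 6-month form asks. The sentence does not describe a strict 3-month recall for admissions, because a future admission cannot lie inside a look-back. Admissions may therefore be recorded separately and in full. The Intervention section also says that other interventions delivered during the trial will be monitored through the patient resource use inventory, which suggests that it was meant to span the trial. Finally, cost-effectiveness is a secondary, exploratory objective.

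Part of this stands, and it rules out several stronger readings that a reader might infer:

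- **That the rest of the index admission is never costed.** This is plausible, because the wording on admissions can be read as sitting inside the 3-month total. The sentence is ambiguous, however, and the loss is not established.
- **That a third of all costs is missing.** The costs of the intervention, serious incidents, containment and staff sickness do not rest on this recall, and incidents are covered without a gap. Only patient-reported service use is exposed.
- **That the main expected saving is lost.** The protocol speaks only of a potential for savings from shorter admission, and it gives prominence to incident and staff-sickness costs as well.
- **That the loss is about £12,000 per patient.** The Background figure (over £12,000) is for a whole admission. Part of that stay precedes baseline and falls in the baseline window.

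What does not stand is the suggestion that this is only omitted detail. The article states both the visit times and the look-back, and together they leave a gap. It describes no 3-month patient contact for this measure, no recall since the last visit and no rule for months 0–3. Even if admissions are fully recorded, community, primary and social care in those months remains uncovered, although a societal perspective is claimed.

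**Conclusion.** The point holds in limited form. Followed literally, the stated schedule leaves patient-reported health and social care use in months 0–3 uncollected in both arms, with admissions a possible exception. This is 33% of follow-up time and 50% of the intervention period; these are shares of time, not of cost. Patient-level costs and QALYs would then cover different periods, and the incremental cost could be biased in either direction by an amount that cannot be computed from the document.

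This rests on two assumptions: that the 3-month look-back applies at every visit, including the 6-month one, and that QALYs run over 0–9 months. The second is inferred from the EQ-5D-5L visits. The primary outcomes are not affected. The schedule should be corrected because the change is cheap and the data cannot be recovered reliably later.

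**What to change.** 1. At the 6-month visit, ask about resource use since baseline, recorded separately for months 0–3 and 3–6. Keep the 3-month look-back at baseline and 9 months.
2. Replace the ambiguous wording on admissions with a statement that all inpatient days from baseline are counted, including the remainder of the index admission.
3. State one common horizon of 0–9 months for costs and QALYs.

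**Cost.** A reworded 6-month form and a few sentences of text. The downside is a 6-month recall at that visit for non-inpatient items, with the recall error that brings.

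**Optional extra.** Index-admission dates could be taken from Trust records for consenting patients. This would firm up the inpatient days, but it departs from the stated preference for self-report and may need added consent and an amendment reviewed by the sponsor and the ethics committee. The main fix does not depend on it.

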## Methods

### Trial design

The study is a single blind, pragmatic, cluster randomised controlled trial. The TULIPS model will be delivered at the ward level (cluster) and compared to treatment as usual within a superiority framework, using a one-to-one allocation ratio, with minimisation based on Trust and ward gender (male/female/mixed). The trial will include a 9-month internal pilot which will have clearly defined stop/go criteria. The comparator was selected on the basis of pragmatics and difficulty in identifying a suitable control comparator.

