In addition to delivering the stepped model of care, the psychologist will also deliver fortnightly group-based, staff reflective practice sessions of one-hour duration and fortnightly team formulation sessions of one-hour duration. Note that these team formulation meetings are separate and in addition to level one formulations and are about a group of staff coming together to reflect on their current and future work with a patient. Decisions about which patients to discuss during these meetings should be based on staff request. However, the psychologist should ensure that meetings do not focus solely on high risk patients as those with lower risk who are less problematic for staff may be excluded. The psychologist will also attend ward MDT meetings. The number of MDT meetings attended, and frequency will be determined in collaboration with senior nursing and medical staff.

The intervention period will run over a period of 6-months and wards randomly assigned to receive the intervention will employ a Psychologist NHS Band 8a or 8b on the ward for 0.5FTE for 7 months to support intervention delivery.

No restrictions will be placed on other care and interventions that are delivered during the trial, but we will attempt to monitor other interventions delivered to patients including other psychological intervention as part of the patient resource use inventory (see outcome measures section below). We will also record any dedicated psychological resource for both intervention and control wards in the study in terms of whole-time equivalent resource and banding.

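### Unit costs not available for 2019/20 are to be uprated with the Retail Price Index, a general household-price index, although most of the costs follow health-sector pay and prices

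*Protocol article*

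**What the plan says.** All the costing text is in the protocol article, mainly under Health economic evaluation.

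- Scope: "Medical costs that will be assessed include costs of the interventions, inpatient care and medication use". The perspective is societal, "incorporating costs borne by the NHS, personal and social services, criminal justice system and education authorities".
- Sources: "Unit costs for each type of service will be derived from local and national databases and statistics".
- Price adjustment: "Any unit costs not available for this price year will be inflated to 2019/20 prices using the Retail Price Index (RPI"). No price year is named before this sentence. A reference is cited for the index but is not available here, and the article gives no reason of its own for the choice.
- Serious incidents: "Unit costs of serious incidents are not readily available and would be derived by estimating the resources that are typically used" to deal with them. Containment is costed from health professionals' time.
- Sensitivity: "Sensitivity analyses will be conducted around unit costs and numbers of incidents as well as different methods of dealing with missing data".
- Intervention section: an intervention ward "will employ a Psychologist NHS Band 8a or 8b on the ward for 0.5FTE for 7 months".

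**The concern.** A price index should track the prices it is used to move. The RPI tracks what households buy. Most of the costs in this evaluation are health-sector inputs: psychologist and ward staff time, bed-days and medication. Where such a unit cost is available only for an earlier year, moving it with a retail index leaves it too high or too low by the accumulated gap between the two series. The items that need uprating need not be those that differ most between the arms, so the error does not have to cancel in the incremental cost or the cost per QALY.

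The price year raises a smaller, second question. It is named only in passing and is not related to the period of data collection. The rule also works in one direction: it says how to inflate an older price to 2019/20, but not how to treat a unit cost quoted in later prices, such as a local figure collected during the trial or actual psychologist pay.

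**Working it through.** The article states no unit costs, index values or recruitment dates, so it has no figure to reproduce and no corrected cost can be computed. Three checks are possible.

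**1. Size of an index mismatch on one uprated unit cost.** All inputs are assumptions: health-sector inflation r = 3% a year, a gap g of 1 or 2 points a year between the RPI and a health-sector index, and y years of uprating. The relative error is ((1 + r + g)/(1 + r))^y − 1.

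| Gap g (points a year) | 1 year | 2 years | 3 years |
|---|---|---|---|
| +1 | +0.97% | +1.95% | +2.94% |
| +2 | +1.94% | +3.92% | +5.94% |
| −1 | −0.97% | −1.93% | −2.88% |
| −2 | −1.94% | −3.85% | −5.71% |

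For example, (1.05/1.03)^3 − 1 = 5.94%. The range is therefore about 1% to 6% in either direction. The sign depends on which index rose faster over the years concerned.

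**2. Effect on totals.** Only unit costs without a 2019/20 figure are moved. If they make up a share s of total cost, the total changes by s times the error above. Over 3 years with a gap of +1 to +2 points:

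- s = 25%: 0.25 × 2.94% = 0.74%, to 0.25 × 5.94% = 1.48%
- s = 50%: 0.50 × 2.94% = 1.47%, to 0.50 × 5.94% = 2.97%

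The shares are also assumptions. For the incremental cost, the shift in money is the error multiplied by the between-arm difference in the uprated items alone. It cannot be given as a percentage of the net difference, because the article contains no costs.

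**3. Price year against calendar.** The only dates are registration on 15 May 2019 (Trial Registration number) and publication on 3 February 2022. Assume that 2019/20 ends on 31 March 2020. A 9-month follow-up then falls inside it only if baseline was by about 1 July 2019, 47 days after registration. A 6-month follow-up does so only if baseline was by about 30 September 2019, 138 days after. With 34 wards to recruit (Sample size) and a 9-month internal pilot (Trial design), much of the follow-up probably came later, if recruitment began at or after registration.

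The consequence is limited. If every unit cost is expressed in one base year, moving that year forward by 1 to 3 years at an assumed 2% to 5% inflation multiplies costs in both arms by the same factor, from 1.02 (one year at 2%) to 1.158 (three years at 5%). A common positive factor cannot change the sign of the incremental cost. It matters when the cost per QALY is set against a current threshold or budget.

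**The case against.** The strongest defence is that the rule is a fallback. It applies only to unit costs that lack a 2019/20 figure, and the article does not show how many there are. The perspective extends beyond the NHS, so a health-sector index would not suit every item. Sensitivity analyses around unit costs are planned. These points stand, and they are why the matter is minor. They do not remove it: the planned sensitivity analyses do not name the index, and they leave the base case as it is.

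Three stronger readings are tempting, and the document supports none of them.

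- A reader might infer that old published costs of admissions, incidents and containment are uprated while the psychologist is priced at current pay, which would distort savings against intervention cost. Incident and containment costs are instead built up from resources and staff time. The article does not say whether admission costs need uprating. The Intervention section gives only band, fraction of full time and duration, and nothing about the price year of the pay.
- A reader might state as fact that 2019/20 closed before most follow-up. No recruitment dates are given, and the future tense of a protocol article is not evidence of dates. This remains an inference.
- A reader might conclude that resources used after 2019/20 cannot be valued in that year's prices. They can: later resource use multiplied by 2019/20 unit costs is valid. A single earlier base year is a normalisation, not an error.

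**Conclusion.** The point holds as a small improvement to the economic analysis. The plan commits to a general retail index for older unit costs that, on the health-care side, are mainly staff, inpatient care and medication, and it does so without a stated reason. Under an assumed gap of 1 to 2 points a year over 1 to 3 years, each uprated unit cost is off by about 1% to 6%, with unknown sign. On total cost the figure is about 0.7% to 3.0% if a quarter to a half of costs are uprated over 3 years. Nothing in the document shows that a conclusion on cost-effectiveness would change, and neither primary outcome is touched.

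The price year is secondary. It should be defined and related to data collection, and all unit costs must reach the same year. Calling the price base wrong or outdated as a whole goes further than the text allows.

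**What to change.** Replace the sentence on inflation in the health economic analysis plan with wording such as:

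> Health and social care unit costs not available for the price year will be adjusted to it, up or down, with a health-sector pay and prices index. Non-health items (criminal justice, education) will be adjusted with a general price deflator. The RPI may be kept as a sensitivity analysis.

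Before it, add one sentence that names the price year, says how it relates to the period of data collection, and confirms that every unit cost, including local ones and psychologist pay, is brought to that year. If the RPI is to stay in the base case, give the reason.

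The cost is two sentences and a small amount of extra analysis. No new trial data are needed.
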